**Overall**				
Participant’s characteristics	Date of birth, gender, ethnicity, BMI (height, weight), highest academic qualification (no degree, middle school, high school), labor situation (working, retired, unemployed in rehabilitation status), current profession, weight at birth, week of pregnancy at birth	SAQ	IG, CG	t0
Clinical status	Diagnoses of OA, Diabetes mellitus Type 2, Cardio vascular disease, and if applicable, date of initial diagnosis, in case of OA site (s) and joint (s) of OA diagnosis	SAQ, on-site CRF	IG, CG	t0
	Other diagnosed comorbidities	SAQ, on-site CRF	IG, CG	t0
	Current medication assessed via medication schedule and/or packaging. Also, pre-determined drugs are recorded via the IDB	SAQ IDB On-site CRF	IG, CG	t0, t6, t12
History of exercise participation	Athleticism during childhood and adolescence	SAQ	IG, CG	t0
Outcome expectations	Personal therapy expectations	SAQ	IG, CG	t0
**Primary Outcome measure**	**Clinical Outcomes**			
Physical activity status	Leisure-time physical activity in a typical week (EHIS-PAQ, HEPA Index [38])	SAQ	IG, CG	t0, t3, t6, t12, t18
**Secondary outcome measure**	**Clinical outcomes**			
Physical activity status	Work-related and transport-related physical activity in a typical week (EHIS-PAQ [38])	SAQ	IG; CG	t0, t3, t6, t12, t18
	Actigraph (wGT3X-BT Accelerometer) for 7 days	wGT3X-BT Accelerometer	IG, CG	t0, t6, t12
Health related quality of life	Veterans RAND 12 Item Health Survey (VR12), retrospective 4 weeks [39, 40]	SAQ	IG, CG	t0, t3, t6, t12, t18
Global health assessment	One Item, General Health, of the VR12 [39, 40] to assess global health [41]	SAQ	IG, CG	t0, t3, t6, t12, t18
Overall perceived benefit	Overall perceived satisfaction with the benefit of the intervention [42]	SAQ	IG, CG	t3, t6, t12, t18
Osteoarthritis specific outcomes	Hip Osteoarthritis Outcome Score (HOOS), Knee injury and Osteoarthritis Outcome Score (KOOS)	SAQ	IG, CG (only participants with OA)	t0, t3, t6, t12, t18
	Pain visual analog pain scale (0–10) [42, 43]	SAQ	IG, CG (only participants with OA)	t0, t3, t6, t12, t18
Cardio vascular risk status	10-year risk of myocardial infarction, PROCAM-Score short form [32]	SAQ	IG, CG	t0, t3, t6, t12, t18
Diabetes mellitus risk status	German diabetes risk score [30, 31]	SAQ	IG, CG	t0, t3, t6, t12, t18
Dietary intake	Food Frequency Questionnaire [44]	SAQ	IG, CG	t0, t3, t6, t12, t18
	**Physiological Outcomes**			
Physical performance measures	Spiroergometry: VO_2_ max, respiratory ratio, physical working capacity (Aeroscan GmbH)	Aeroman	IG, CG	t0, t6, t12
	Lower body strength measure: 30 s sit to stand Test (CST) [42, 45]	30 CST	IG; CG	t0, t6, t12
	Electrocardiogram (ECG) (custo med GmbH) to assess heart rate, systolic and diastolic blood pressure at rest and during exercise test	Custo Cardio 300	IG; CG	t0, t6, t12
Body composition	Assessment of body composition (muscle, fat, water distribution) with bioimpedance analysis (SMT medical GmbH & Co.)	BIA101 BIVA	IG, CG	t0, t6, t12
Metabolomics	Capillary blood sample from earlobes on Guthrie cards to assess carnitine, short- and long-chain acylcarnitines, methionine, phenylalanine, tyrosine, valine, leucine, isoleucine, succinylacetone, citrulline	Blood sample	IG, CG	t0, t6, t12
Laboratory data	Fasting blood sample: HbA1c, insulin, fasting glucose, IL-6, CRP, cholesterol, LDL, HDL, triglycerides, miRNAs, adiponectin, leptin, resistin, COMP Urine sample: CTXII	Blood and Urine sample	Sub-sample IG, CG	t0, t6, t12
	**Exercise psychological outcomes**			
Exercise-specific self-efficacy	Multidimensional Self-Efficacy for Exercise Scale: task, coping, and scheduling efficacy [46]	SAQ	IG, CG	t0, t3, t6, t12, t18
Sport and exercise-related self-concordance	Self-concordance of sport- and exercise-related goals: intrinsic, identified, introjected, and extrinsic modes of motivation [47]	SAQ	IG, CG	t0, t3, t6, t12, t18
Physical-activity related health competence	Physical-activity related health competence questionnaire: control of physical load, affect regulation, and self-control [21, 48]	SAQ	IG, CG	t0, t3, t6, t12, t18
Sport- and exercise specific motivational competence	Questionnaire on motivational competence in exercise and sport: knowing one’s own preferences, knowing what to expect in different exercise and sport activities and choosing and arranging an exercise and sport activity [49]	SAQ	IG, CG	t0, t3, t6, t12, t18
Action and coping planning	Exercise planning scales: action plans, coping plans [50]	SAQ	IG, CG	t0, t3, t6, t12, t18
Attitudes towards physical activity	Cognitive and affective attitudes towards physical activity [51]	SAQ	IG, CG	t0, t3, t6, t12, t18
Motives and goals for exercise	Bernese motive and goal inventory [52]	SAQ	IG	Throughout intervention phase 1 (week 7), t6, t12
Fear of movement /(re)injury	Tampa Scale for Kinesiophobia [53]	SAQ	IG, CG	t0, t3, t6, t12, t18
	**Economic Data**			
Unspecific and specific (disease-related) health care costs	Outpatient costs, hospital costs, medication, adjuvants, rehabilitation treatment, medically prescribed supplementary treatments (e.g. hydrotherapy, physiotherapy, massages)	IDB	IG, CG	tm18, tm12, tm6 t6, t12, t18
Unspecific/specific (disease related) periods of disability	Days of disability (overall and related to referred diseases)	IDB	IG, CG	tm18, tm12, tm6 t6, t12, t18
Intervention related costs	Costs for human and physical resources/session	IDB	IG	t6, t18

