## Interventions

Both types of interventions (regular health care offers for CG, *MultiPill-Exercise* for IG), are conducted at the health centers of the statutory health insurance company, in which different kinds of health care programs are offered to customers of the insurance company on a regular basis.

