	**Process evaluation**			
Characteristics of the usual care arm	Questions on utilization of usual care offers	SAQ	CG	t3, t6, t12
Participants’ satisfaction	Modified version of the ZUF-8 Questionnaire to assess participants’ satisfaction with the intervention [54]	SAQ	IG, CG	t3, t6, t12, t18
Participants’ view on the intervention	Qualitative interviews with participants including questions on the appropriateness and quality of the intervention delivery	QI	Sub-sample IG	after last intervention delivery
Treatment fidelity	Field notes for intervention progress (Troubleshooting)	Documentation sheets	Research Team	continuously
	Notes for intervention delivery	Notation sheets	Interventionists	continuously
Characteristics of interventionists	Questionnaires on occupational self-efficacy [55], subjective value attributions [56] and implementation outcomes (acceptability, appropriateness, and feasibility of the intervention) [57]	SAQ	Interventionists	t0, t6
Interventionists’ view on the program	Qualitative interviews with exercise specialists regarding acceptability, practicality, appropriateness and fidelity aspects of the intervention delivery	QI	Interventionists	after last intervention delivery
	Satisfaction with the interventionists’ training [58]	SAQ	Interventionists	after interventionists training
Evaluation of implementation regarding interfaces of the health service innovation	Practitioners’ view on the acceptability, appropriateness, and feasibility of the program and its prescription [57]	SAQ	Health insurance company (APS)	during recruitment
	Mode of access to the program	Telephone screening	IG, CG	during recruitment
Evaluation of implementation regarding the interface with community-based exercise offers	Qualitative interviews with participants and employees of the health insurance company	QI	Sub-sample IG and interventionists	after last intervention delivery
Adherence to exercise training	Summarized number of attended training sessions and reported trainings sessions according to training logs of the exercise specialists and participants (IG)	Training logs, on-site reporting sheet (IG); SAQ, IDB (for CG only)	IG, CG	t3, t6

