### Standard Care (CG)

The standard care of statutory health insurance company offers every insured person the opportunity to participate in health offers, provided and conducted by employed professionals from the health insurance company, free of charge. For a more detailed information of the German health care see Struckmann, Boerma [68].

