Participants of the CG are requested to select from the standard care offers of the statutory health insurance company. Potential offers are in the field of nutrition, exercise and special DMPs, general health and ‘fit and active’. The exercise offers last 8–12 weeks. Participants of the CG will be provided with options by an exercise specialist of the insurance company and will then be able to enroll in the selected offers. Over the study period, participants can attend two different offers, as foreseen in regular care. The combination and choice of offers can be freely arranged according to the participants' own preferences. An exception applies to participants with a physician’s recommendation for prevention programs. With this recommendation, they can also take part in additional offers. All offers will be provided by exercise specialists from the statutory health insurance company and are based on their own manual, which are adhered to in a restrictive manner. Nutrition offers include: a workshop that focuses on education, particular recommended foods and the right combination of foods to induce positive health effects. It also highlights general principles of a balanced diet and practical tips, such that the knowledge can be implemented in the kitchen. The second offer, ‘body and soul in balance’, fosters active weight loss and mindful eating. The aim here is on sustainable change in diet, with more desire for exercise and fun within a lifestyle that relies on personal responsibility, knowledge and conscious decisions. The disease specific DMPs for CVDs include: ‘All the best for your heart’. This offer teaches the basics of avoiding and reducing coronary heart disease. ‘Fourfold increase in quality of life’ (DMP for DMT2) aims to increase everyday activities, giving information on avoiding obesity, recovery from physical and mental stress and information on special foot care for diabetes. Also, light gymnastics, light walking and a special strength-endurance training can be chosen. A focus of the general health offers is to reduce physical inactivity and to strengthen physical health resources. The offer includes courses to increase fitness, flexibility, endurance and strength. Included courses are: Clever-Walking, Fit-Mix, Functional Training, Easy Running, Outdoor Fitness, Back-Fit, and Back-Power.

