##### Economic data (insurance data base; firm software)

Economic data comprise unspecific and specific disease related health care costs. Intervention related costs for the exercise program will be taken into consideration as well.

Unspecific health care costs (overall costs): Outpatient acute care, hospital costs, rehabilitative treatment, medically prescribed supplementary treatments (*e.g.* hydrotherapy, physiotherapy, massages), adjuvants, costs related to periods of disability, medication and intervention related costs.

Specific medical costs refer to the costs of the diagnoses CVD, DMT2, hip and/or knee OA, OW/OB and the intervention costs.

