#### Economic evaluation

The costs (including the costs for the intervention) will be related to the differences between the groups in quality adjusted life years (QALYs) (Eq. 1) and health related effects (e.g. HOOS Index, PROCAM-Score: Eq. 2).

Equation 1: Cost-Utility Analysis (CUA) = Incremental Cost Utility Ratio (ICUR)1$$\mathrm{ICUR }=\frac{\Delta Cost}{\Delta QALYs}$$

Equation 2: Cost-Effectiveness Analysis (CEA) = Incremental Cost-Effectiveness Ratio (ICER)2$$\mathrm{ICER }=\frac{\Delta Cost}{\Delta Effect}$$

Uncertainty sampling in the ICER will be handled using nonparametric bootstrapping and graphically presented on a cost-effectiveness plane. We will examine cost-effectiveness and cost-utility from a societal and health care perspective.

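### Programme costs are collected per session for the intervention group only, so the cost difference in the ICER and ICUR leaves out the insurer-run courses that form the control arm

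*Protocol article*

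**What the plan says.** The Economic Data block of Table 2 has three rows. The first, health care costs, reads "Outpatient costs, hospital costs, medication, adjuvants, rehabilitation treatment, medically prescribed supplementary treatments" and covers IG and CG. The second, days of disability, also covers IG and CG. The third, intervention related costs, is described as "Costs for human and physical resources/session" and covers the IG only, at t6 and t18. All three come from the insurance database.

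The section on economic data says: "Intervention related costs for the exercise program will be taken into consideration as well". Its definition of overall costs then includes intervention related costs without naming an arm, and also counts costs arising from periods of disability.

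The Interventions section treats the control offers as an intervention in their own right ("Both types of interventions (regular health care offers for CG", it begins) and places both arms' programmes in the insurer's health centres. Under Standard Care the offers are "provided and conducted by employed professionals from the health insurance company, free of charge". On quantity, the plan states: "Over the study period, participants can attend two different offers, as foreseen in regular care". A physician's recommendation opens the way to more. Exercise offers last 8 to 12 weeks.

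Use of these courses is recorded, but as process evaluation. Table 2 lists "Questions on utilization of usual care offers" for the CG at t3, t6 and t12, and CG attendance from questionnaire and insurance database at t3 and t6. The Limitations section adds that every follow-up questionnaire asks about other health care offers taken up.

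The Economic evaluation section divides the between-group cost difference, intervention costs included, by the difference in QALYs or in a health effect. It states: "We will examine cost-effectiveness and cost-utility from a societal and health care perspective".

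**The concern.** The economic question is whether MultiPill-Exercise is worth its cost compared with what the insurer already offers. That offer uses the same kind of resources as the new programme: employed staff and health centre facilities. It is free to the participant, not to the payer. If one arm's programme is costed per session and the other's is not, the numerator no longer answers that question.

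This is not detail left to a fuller document. The sample column is filled in for every economic row, and one row differs from the other two. The text repeats the restriction by tying intervention costs to the exercise programme.

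The error would be systematic. The planned bootstrap resamples the recorded costs, so it cannot reveal a component that was never recorded. Economic efficiency is one of the research questions named in the Discussion, and the article says a successful programme will be established in the insurer's care system.

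**Working it through.** The article states no cost, ICER or ICUR, so there is no figure of its own to reproduce. The check is algebraic.

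**Notation, per participant**
- P_IG: cost of MultiPill-Exercise (recorded; Table 2, IG only).
- P_CG: cost of the insurer-run courses used by the CG (no clear cost row).
- X_IG: cost of extra insurer offers used by the IG (allowed under Limitations; no clear cost row).
- H_IG, H_CG: the other care and disability costs (recorded in both arms).

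**Cost difference as the rows are written**

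ΔCost_recorded = P_IG + (H_IG − H_CG)

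**Cost difference with all insurer-run programmes counted**

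ΔCost_full = (P_IG + X_IG) − P_CG + (H_IG − H_CG)

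**Error in the numerator**

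ΔCost_recorded − ΔCost_full = P_CG − X_IG

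The ratio is therefore shifted by (P_CG − X_IG)/ΔEffect. With ΔEffect scored so that positive means benefit, the shift goes against MultiPill-Exercise when it is more effective and P_CG exceeds X_IG.

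**Illustration.** Set P_IG = 1, P_CG = r, X_IG = 0 and H_IG = H_CG. The values of r are assumptions. The inflation factor is 1/(1 − r):

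| r (assumed) | Recorded ΔCost | Full ΔCost | Factor | Inflation |
|---|---|---|---|---|
| 0.10 | 1 | 0.90 | 1.11 | 11% |
| 0.25 | 1 | 0.75 | 1.33 | 33% |
| 0.50 | 1 | 0.50 | 2.00 | 100% |

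If the IG also saved 0.2 of P_IG in other care (a further assumption), the factor is (1 − 0.2)/(1 − r − 0.2):
- r = 0.10: 0.80/0.70 = 1.14
- r = 0.25: 0.80/0.55 = 1.45
- r = 0.50: 0.80/0.30 = 2.67

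The same omission weighs more as the net cost difference shrinks. Any X_IG above zero reduces the error.

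**Can the planned data supply the missing quantities?**

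| Item | Arm | Time points |
|---|---|---|
| Utilisation of usual care offers (Table 2) | CG | t3, t6, t12 |
| CG attendance, questionnaire and insurance database (Table 2) | CG | t3, t6 |
| Extra offers (Limitations) | IG and CG | all follow-up questionnaires |
| Health care costs after baseline (Table 2) | IG and CG | t6, t12, t18 |

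Quantities are largely planned. The Table 2 utilisation item omits the IG and t18, whereas the Limitations text covers both. No section attaches a unit cost to any of these quantities.

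**Perspective.** The listed items beyond direct care are disability days and their costs, in both arms. No out-of-pocket, travel or time costs of participants are listed, although the IG may have up to three on-site appointments a week.

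**The case against.** **The control courses might be costed after all.** The overall cost definition includes intervention related costs without naming an arm, and the Interventions section calls both programmes interventions. The prescribed-treatment category is open-ended, some control offers follow a physician's recommendation, and the article does not say how the insurer books its courses. This stands to a degree: a reader might infer that the plan sets control courses at zero, and no sentence says so. But the one row that defines per-session costing names the IG alone, and the examples of prescribed treatments (hydrotherapy, physiotherapy, massages) are not the insurer's in-house courses. Recording use for process evaluation is not a plan to cost it.

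**The cost difference is more than programme cost.** A reader might infer that ΔCost reduces to the IG programme cost minus nothing. It does not: other care and disability are collected in both arms. Only the programme component is one-sided.

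**The size is unknown.** It is tempting to put euros per QALY on the bias. The article gives no session price, no session count for the control courses and no expected QALY gain, and one nutrition offer is described only as a workshop. Such a figure would rest wholly on assumptions and would ignore the offset from extra offers used by the IG. This objection stands in full.

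**The societal perspective has data.** A reader might infer that it has none. Disability days are collected in both arms and their costs are counted, so the support is incomplete rather than absent.

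**It is a secondary analysis.** True: the primary endpoint, its test and the sample size are untouched.

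**Conclusion.** The point holds for the programme-cost component. As written, the numerator of the ICER and ICUR contains the cost of MultiPill-Exercise but not that of the control programme, and it is overstated by P_CG − X_IG. The direction is against MultiPill-Exercise, provided that it is more effective and that control course costs exceed those of the extra offers used by the IG. The inflation of 11%, 33% or 100% is illustrative only: it assumes equal other costs, no extra offers in the IG, and control programme cost at 10%, 25% or 50% of the IG's. The document does not allow the actual size to be determined.

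On perspective, the listed data support an insurer or health care view plus disability-related productivity loss. An unqualified societal label claims more than that, because no participant-borne costs are listed.

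This should be corrected before the economic analysis. It does not threaten the trial's main result.

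**What to change.** 1. In Table 2, change the sample for intervention related costs from IG to IG and CG, and reword the matching sentence in the economic data section so that it covers the insurer-run programmes of both arms.
2. Cost every insurer-run course used in either arm, including extra offers taken by the IG, with the same per-session method for staff and physical resources. Take quantities from the planned utilisation and attendance data.
3. Extend the Table 2 utilisation item to the IG and to t18, as the Limitations section already implies, so that quantities cover the same period as costs.
4. Limit the societal label to an insurer or health care perspective plus disability-related productivity loss, or add participant-borne cost items if a wider claim is wanted.

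The cost is modest. The insurer must supply unit costs for its own courses, one questionnaire item is extended, and the analysis takes a little more work. The stated perspective becomes narrower unless items are added. Neither the design nor the sample size changes.

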	**Process evaluation**			
Characteristics of the usual care arm	Questions on utilization of usual care offers	SAQ	CG	t3, t6, t12
Participants’ satisfaction	Modified version of the ZUF-8 Questionnaire to assess participants’ satisfaction with the intervention [54]	SAQ	IG, CG	t3, t6, t12, t18
Participants’ view on the intervention	Qualitative interviews with participants including questions on the appropriateness and quality of the intervention delivery	QI	Sub-sample IG	after last intervention delivery
Treatment fidelity	Field notes for intervention progress (Troubleshooting)	Documentation sheets	Research Team	continuously
	Notes for intervention delivery	Notation sheets	Interventionists	continuously
Characteristics of interventionists	Questionnaires on occupational self-efficacy [55], subjective value attributions [56] and implementation outcomes (acceptability, appropriateness, and feasibility of the intervention) [57]	SAQ	Interventionists	t0, t6
Interventionists’ view on the program	Qualitative interviews with exercise specialists regarding acceptability, practicality, appropriateness and fidelity aspects of the intervention delivery	QI	Interventionists	after last intervention delivery
	Satisfaction with the interventionists’ training [58]	SAQ	Interventionists	after interventionists training
Evaluation of implementation regarding interfaces of the health service innovation	Practitioners’ view on the acceptability, appropriateness, and feasibility of the program and its prescription [57]	SAQ	Health insurance company (APS)	during recruitment
	Mode of access to the program	Telephone screening	IG, CG	during recruitment
Evaluation of implementation regarding the interface with community-based exercise offers	Qualitative interviews with participants and employees of the health insurance company	QI	Sub-sample IG and interventionists	after last intervention delivery
Adherence to exercise training	Summarized number of attended training sessions and reported trainings sessions according to training logs of the exercise specialists and participants (IG)	Training logs, on-site reporting sheet (IG); SAQ, IDB (for CG only)	IG, CG	t3, t6
	**Safety and Adverse Events**			
Adverse events and side-effects	Summarized number and details of adverse events and side-effects according to training log and case report form	Training logs, on-site CRF, SAQ	IG	t3, t6

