## Methods

### Study design

The study will be conducted in the context of health service research. The feasibility of the intervention and an exploratory analysis of its effects on health outcomes were tested in a non-controlled pilot study (DRKS00016702). Results have been used to optimize the current study design, for example through putting more emphasis on nutrition, extending supervision time during the study period (24 weeks of supervised machine-based training instead of only 12 weeks) and integrating videos into the exercise sessions at home. The current study is now designed as a multi-site randomized controlled superiority pragmatic trial with two parallel groups. It evaluates the effectiveness, efficiency and safety of the 24-week comprehensive lifestyle intervention *MultiPill-Exercise* in comparison to the regular health care offer of a statutory health insurance company. Participants will be randomized to intervention and control group with an allocation ratio of 1:1. Measurements will be taken at baseline (t0), three months (t3), six months (t6), 12 months (t12) and 18 months (t18). The study was prospectively registered in the German Clinical Trial Register (DRKS00025033) and is documented according to the completed Standard Protocol Items: The recommendations for interventional trials (SPIRIT) checklist [27] and the Pragmatic-Explanatory Continuum Indicator Summary (PRECIS)-2 checklist [28] are available as supplements (Additional files 1 and 2).

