##### Safety: Adverse events and side-effects

The rating of the safety of the intervention is documented by listing exercise related adverse events or side-effects by different parties: The exercise specialists of the study sites will document all potential adverse events of the exercise of which they have become beware of. Participants are urged to report adverse events or side-effects to their guide or to report them in their training-log. Exercise-related adverse events are also retrospectively assessed via the online questionnaire at t3 and t6. All participants can further contact the study physician of the university hospital at any time as outlined in the participant information sheet. The standard adverse events and severe adverse event form of clinical trials will be implemented in the SecuTrial database.

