## Discussion

Within this protocol, a comprehensive PA promotion program for people with multiple NCDs is introduced. *MultiPill-Exercise* has been designed to address insufficient active people suffering of multiple NCDs, including a holistic approach. Several research questions will be evaluated: (1) The effectiveness of a comprehensive lifestyle and exercise intervention specifically designed for patients with multimorbidity on physical activity status (primary outcome of the trial); (2) the effectiveness of the intervention on generic and disease specific health outcomes, (3) the effectiveness of the intervention regarding the prevention and progression of specific diseases (4); the economic efficiency of the lifestyle intervention in the treatment of several NCDs; (5) the feasibility of implementation of the intervention into patient care in a regular health care setting including safety aspects of the intervention. (1) to (4) will be evaluated in the short and long term in comparison to typical health care offers.

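### Table 2 tabulates adverse events for the intervention group only, while the Study design section promises a safety evaluation against regular care; the sections need reconciling and the same items should go to both arms

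*Protocol article*

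**What the plan says.** Four places in the protocol article bear on this point.

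- **Study design.** Of the trial it says: "It evaluates the effectiveness, efficiency and safety of the 24-week comprehensive lifestyle intervention". The same sentence goes on to name the comparator: "in comparison to the regular health care offer of a statutory health insurance company".
- **Table 2, Safety and Adverse Events.** The outcome is "Summarized number and details of adverse events and side-effects according to training log and case report form". The data sources are "Training logs, on-site CRF, SAQ", the sample is IG, and the collection points are t3 and t6.
- **Safety: Adverse events and side-effects.** Exercise specialists at the sites document events they become aware of. In addition, "Participants are urged to report adverse events or side-effects to their guide or to report them in their training-log". A questionnaire is also named: "Exercise-related adverse events are also retrospectively assessed via the online questionnaire at t3 and t6". No arm is given for it. Finally, "All participants can further contact the study physician of the university hospital at any time", and standard adverse-event and severe-adverse-event forms are set up in the study database.
- **Discussion.** Safety appears within the fifth research question, "the feasibility of implementation of the intervention into patient care in a regular health care setting including safety aspects of the intervention". Only questions (1) to (4) are said to be evaluated against typical health care offers.

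**The concern.** Study design attaches a comparator to safety, but the outcome table assigns adverse-event data to one arm. A later analysis plan cannot repair this, because it cannot compare data that were not collected.

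A comparator matters in this population. Participants have, or are at risk of, osteoarthritis, obesity, diabetes or cardiovascular disease, so musculoskeletal and cardiac symptoms can be expected without any training. Controls may choose courses in endurance, strength or running, so exercise-related events can occur there too. Both arms may also use other health care offers (Limitations), so an event in an IG participant need not come from the programme. A one-arm count cannot separate these sources.

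At stake is a stated purpose of the trial. The Abstract calls safety an open question, the Objectives list it as a secondary aim, and the Conclusion says the results will assess it. The Data Availability section says a successful programme will be established in the insurer's care.

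**Working it through.** The plan gives no figure for safety. Its only sample-size result, 123 evaluable participants per group, concerns the primary endpoint and has no bearing here. The check is therefore mainly textual.

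**Step 1. Is the IG entry in Table 2 deliberate?** The adherence row, directly above the adverse-event row, lists both arms and names separate data sources for controls. The table therefore distinguishes the arms on purpose, and the IG entry cannot be dismissed as table shorthand.

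**Step 2. Could controls have supplied the data?** Yes. Self-administered questionnaires are an adverse-event source in Table 2, and controls complete such questionnaires at t3 and t6 for many other outcomes.

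**Step 3. Do the sections agree?**

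| Section | Is safety comparative? | Arms supplying adverse-event data |
|---|---|---|
| Study design | Yes, against regular care | Not stated |
| Table 2 | Not stated | IG only |
| Safety section | Not stated | Guide and training log belong to IG; questionnaire arm not stated; physician contact open to all |
| Discussion | Not among the comparative questions | Not stated |

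They do not. Study design conflicts with the Discussion on whether safety is comparative. Table 2 is narrower than the safety section can be read.

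**Step 4. What does one-arm collection yield?** Only a one-arm rate. If no events of a given kind were seen, the one-sided 95% upper bound would be 1 − 0.05^(1/n):

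- n = 160: 1.9%
- n = 128: 2.3%

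There is no control rate to set beside it.

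**Step 5. What would two-arm collection yield?** Arm sizes come from Recruitment (160 per arm) and from the 20% dropout under Sample size (320 × 0.8 = 256, so 128 per arm). The article gives no event rates, so the rates below are assumptions. The half-width is 1.96 × √[p₁(1−p₁)/n + p₂(1−p₂)/n].

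For 20% v 10%:

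- n = 160: √(0.16/160 + 0.09/160) = 0.0395; × 1.96 = 7.7 points
- n = 128: √(0.16/128 + 0.09/128) = 0.0442; × 1.96 = 8.7 points

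Range over other assumed rates:

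| Assumed rates | Half-width, n = 160 | Half-width, n = 128 | Power, n = 160 | Power, n = 128 |
|---|---|---|---|---|
| 10% v 5% | 5.7 points | 6.4 points | 0.40 | 0.33 |
| 20% v 10% | 7.7 points | 8.7 points | 0.71 | 0.61 |
| 35% v 20% | 9.6 points | 10.8 points | 0.86 | 0.77 |

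Power is for a two-sided 5% test. It is modest for small differences, but an interval of this width is still informative, and Table 2 as it stands permits none.

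**The case against.** A reader might infer that control events go uncollected and that no safety comparison of any kind is possible. The article does not support that.

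- The questionnaire sentence in the safety section names no arm, all participants may contact the study physician, and the database forms are not stated to be limited to IG. The insurer's exercise specialists also deliver the control offers. Control events may therefore reach the study team.
- Table 2 gives harm-relevant data for both arms: KOOS/HOOS and pain scores in participants with osteoarthritis, back pain, hospital and outpatient costs, medication and disability days.

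These points stand as limits on the claim. They do not remove it. None of these data is planned as a comparative adverse-event outcome, physician contact is unsolicited, and the guide and training log exist only in IG. If the safety section does mean both arms, Table 2 is wrong and still needs correcting.

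It can also be argued that safety was meant only as a description of the programme. The Discussion places it under feasibility, and the safety section speaks of listing exercise-related events. On that reading IG-only collection is coherent and the Study design sentence is the loose one. This is a fair reading, and it is why withdrawing that wording is an acceptable fallback.

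A reader might also infer that whoever reports an event decides whether exercise caused it. The article does not say who judges relatedness, and it may leave that to the full protocol, so the point does not rest on it.

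**Conclusion.** The concern holds in limited form. The article contradicts itself on whether safety is comparative and is unclear on which arms answer the adverse-event items. As tabulated, no between-arm adverse-event difference is planned or estimable. Indirect harm-relevant data in both arms soften this but do not replace an adverse-event comparison.

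The primary endpoint is unaffected; the weakness lies in one stated aim. The textual finding needs no assumptions. The half-widths of 7.7 and 8.7 points rest on assumed rates of 20% and 10% and only show what precision the trial's size could give.

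**What to change.** 1. Put identical adverse-event items (all events, seriousness, relation to any exercise) to both arms in the existing t3 and t6 online questionnaire.
2. Change the sample in the Table 2 adverse-event row to IG, CG, and name both arms in the safety section.
3. Base the between-arm comparison on this common source only, reported as a difference with its confidence interval.
4. Report events from training logs, guides and exercise specialists separately, as IG-only description. Pooling them would add events from channels controls do not share.
5. Align the Discussion with Study design. If control collection is not possible, withdraw the comparative safety wording in Study design instead.

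**Cost.** A slightly longer control questionnaire and an ethics notification. First inclusion was planned for April 2022 and the article appeared in June 2022, so the first t3 questionnaires fall due around July 2022 and some may be missed. Some reporting imbalance would remain even with identical items, because IG participants are urged to report events and keep logs that may prompt recall.
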